#### Exploratory outcomes

2.7.3

Alterations in brain FC (as measured by total integration) across various groups. Additionally, changes in the strength of FC before and after treatment will serve as exploratory outcome measures to explore the mechanisms underlying TMS treatment for ET. MRI will be conducted at baseline, on D10, and at W4.

### Sample size

2.8

This pilot study involves a small number of patients and aims to assess the practicality and feasibility of the methodologies intended for use in a subsequent, larger, and more comprehensive investigation, as well as to identify any unforeseen challenges. Badran (46) indicated that a sample size of five patients per group is sufficient to ascertain whether a larger multicenter trial should be pursued. Additionally, Popa (29) proposed that 11 participants per group are adequate for evaluating feasibility in a pilot study. Drawing on prior research (28), our objective is to recruit eight patients per group. The findings of this study are expected to provide preliminary insights into the safety and feasibility of dual-target TMS in patients with ET and will inform the estimation of sample size and the conduct of a power calculation for the planning of a Phase 3 trial.

### Randomization

2.9

In this study, a simple randomization method will be used to generate 30 random numbers utilizing a table of random numbers, commencing from row 2 and column 3, with every two adjacent numbers considered as a single random number. These random numbers will be divided by three to determine the remainder, which will categorize participants into three groups: a remainder of zero for the double-target group, one for the single-target group, and two for the sham stimulus group. The pre-generated random numbers will be securely placed in opaque, sealed envelopes, which will be stored and maintained by the lead investigator. At the initiation of treatment, one envelope will be opened to ascertain the group assignment of participants in the order of their enrollment. Throughout the duration of the study, both the participants and the assessors will remain unaware of the group assignments.

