**Methods:**

Twenty-four patients with ET will be randomly assigned to three groups: dual-target stimulation, single-target stimulation, or sham stimulation. The single-target stimulation group will receive stimulation of the right cerebellar hemisphere for 10 days, whereas the dual-target stimulation group will be given stimulation of both the left M1 cortex and the right cerebellar hemisphere. The sham stimulation group will be given sham stimulation for 10 days. Tremor will be assessed using both the subjective The Essential Tremor Rating Assessment Scale (TETRAS) and objective accelerometer-based tremor analysis. at baseline (before stimulation), after the first, fifth, tenth days of treatment (D1, 5, 10), 24 h after 10 days of treatment (D10-24 h), and 1, 2, 3, and 4 weeks after stimulation (W1, 2, 3, 4).

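### Simple randomization by remainder after division by three does not ensure, and very probably will not give, the stated eight patients per group

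*Protocol article*

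**What the plan says.** All references are to the protocol article.

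- **Size.** The abstract (Methods) states: "Twenty-four patients with ET will be randomly assigned to three groups". Section 2.8 (Sample size) adds that "our objective is to recruit eight patients per group".
- **Method.** Section 2.9 (Randomization) states that "a simple randomization method will be used to generate 30 random numbers utilizing a table of random numbers", "with every two adjacent numbers considered as a single random number".
- **Allocation rule.** In the same section: "These random numbers will be divided by three to determine the remainder", with "a remainder of zero for the double-target group, one for the single-target group, and two for the sham stimulus group".
- **Use of the list.** At the start of treatment, "one envelope will be opened to ascertain the group assignment of participants in the order of their enrollment".

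Section 2.9 mentions no block, stratum, quota or replacement rule. It does not say why 30 numbers are drawn for 24 patients. Section 2.8 gives no power calculation. It cites one earlier study for the view that five patients per group suffice to decide on a larger trial.

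**The concern.** The size statement is per group, but the allocation rule controls no group's size. Each envelope is an independent draw, so the arm sizes are multinomial and only the total is fixed. The Randomization section gives the algorithm down to the starting row and column of the table. The gap is therefore not a detail that an article leaves to a fuller document: the algorithm as described does not produce the stated arm sizes.

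What is at stake is precision and the usefulness of the pilot. Adherence and serious adverse event rates are secondary outcomes (section 2.7.2), and section 2.8 says the results will inform the sample size of a Phase 3 trial. An arm of four or five patients supports such estimates poorly.

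**Working it through.** **Inputs.** Total 24 (abstract), 8 per group (section 2.8), 30 numbers, two-digit form and remainder rule (section 2.9). The plan's own figure is consistent: 3 × 8 = 24.

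**Allocation probabilities.** Of the numbers 00 to 99, 34 leave remainder 0, 33 leave 1 and 33 leave 2, so p = (0.34, 0.33, 0.33). If 00 is not used, each is 33/99 = 1/3.

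**Formula.** P(a, b, c) = 24!/(a! b! c!) × p₀ᵃ p₁ᵇ p₂ᶜ, summed exactly over all splits with a + b + c = 24.

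**Exact 8/8/8.** With equal thirds: 24!/(8!)³ ÷ 3²⁴ = 9,465,511,770 ÷ 282,429,536,481 = 3.35%.

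| Event, n = 24 | p = 1/3 each | p = 0.34/0.33/0.33 |
|---|---|---|
| 8/8/8 | 3.35% | 3.34% |
| All arms 7 to 9 | 21.2% | 21.2% |
| At least one arm ≤ 5 | 40.4% | 40.5% |
| At least one arm ≤ 4 | 17.7% | 17.8% |
| One named arm ≤ 5 | 13.8% | 12.4% (dual-target), 14.6% (each other arm) |
| Expected smallest / largest arm | 5.7 / 10.4 | 5.7 / 10.4 |

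A simulation of 400,000 trials with equal thirds gave 3.3% for 8/8/8 and 40.5% for an arm of five or fewer. The slight excess of remainder 0 makes no practical difference.

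**Do the 30 numbers help?** Suppose the extra six were a reserve, with surplus envelopes skipped once an arm is full. That rule is not stated and does not fit opening envelopes in enrollment order. Even so, the same enumeration with n = 30 gives P(at least eight of every arm) = 51.8% with equal thirds, or 51.7% with 0.34/0.33/0.33. About 48% of lists could not supply eight per arm.

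**Cost in precision.** Take the variance of a two-arm contrast as proportional to 1/n₁ + 1/n₂ (equal outcome variances, complete data). Relative to 8 v 8, the ratio is (1/n₁ + 1/n₂)/(1/8 + 1/8).

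- 5 v 8: (0.200 + 0.125)/0.250 = 1.30.
- A 5/9/10 split: 5 v 9 gives 1.24, 5 v 10 gives 1.20, and 9 v 10 gives 0.84.

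Over the exact distribution for dual-target v sham (p = 0.34/0.33/0.33), the median ratio is 1.067, the mean about 1.10, and a ratio of 1.30 or more occurs in about 16% of trials. With equal thirds, these are 1.067, 1.11 and 17%.

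**The case against.** The case for leaving the procedure alone has several parts, and much of it stands.

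- **Simple randomization is a valid method.** This is right. Chance imbalance in arm sizes does not bias the comparison, and unrestricted draws are the least predictable choice when operators know the allocation.
- **Eight per group is an objective, not a guarantee.** This is partly right. A reader might infer that the rule cannot give 8/8/8. It can, in about 3% of trials. But a target reached that rarely should not be stated per group without comment.
- **Five in an arm may be enough.** Section 2.8 cites five per group as sufficient, so an arm of exactly five meets that benchmark. The stricter event, an arm of four or fewer, has probability about 18%, and the 40% applies to any of three arms rather than one named arm.
- **The precision loss is modest.** This stands. A 30% inflation is not typical: the median is about 7%, and a small arm makes the contrast between the other two more precise. No power calculation is undermined, because none is given.

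A reader might also infer that the sequence can be rebuilt, because the starting row and column and the remainder rule are published during recruitment and the envelopes are "stored and maintained by the lead investigator". The article does not support that. It does not name the table of random numbers, it specifies sealed opaque envelopes opened at the start of treatment, and it does not say that the lead investigator enrolls patients.

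**Conclusion.** The point holds as an inconsistency between the stated arm size and the allocation rule. Eight per group is a property that the design does not have: an exact split has probability about 3%, and even arms all within one of eight occur only about 21% of the time. The 30 pre-generated numbers do not close the gap, and their relation to 24 patients needs explaining.

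The consequence is lost precision and thinner per-arm adherence and safety data, not bias. It should be fixed, but it does not invalidate the trial. The figures assume exactly 24 patients allocated by 24 independent draws, with no unstated balancing rule.

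**What to change.** **Preferred.** For envelopes not yet opened, replace the remainder list with a computer-generated permuted-block list using mixed blocks of 3 and 6, prepared by someone not involved in enrollment or assessment. Keep the allocations already made and record the date of the change. From then on, the new list adds a difference of at most two between any two arms, since a part-used block of 6 holds at most two of each arm.

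Do not force the total to 8/8/8. Recruitment is under way (section 2.1), so an arm may already exceed eight. Forcing the total would also require an unblinded tally and make the last assignments predictable.

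**If the list stays.** Restate the size as 24 in total with arm sizes left to chance, and reconcile the 30 numbers with the 24 patients.

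**Cost.** The first option takes a revised paragraph, a new set of envelopes and a dated record of the change, with no extra patients. Its downside is that blocks are slightly more predictable to the operators, who are not among the blinded parties in section 2.10. Mixed block sizes limit this. The second option is a wording change only and leaves the imbalance in place.

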### Blinding

2.10

This study will follow a patient-assessor blinded clinical design. To enhance the validity of the stimulation procedures, all participants will undergo two rounds of stimulation, each targeting both the left M1 region and the right cerebellar hemisphere. In the dual-target stimulation group, during the first round, actual stimulation will be administered to the cerebellum while the cortical coil will be oriented at a 90° angle to prevent effective stimulation; during the second round, this approach will be reversed. The single-target stimulation group will also go through two rounds, with the first round focused on true cerebellar stimulation and the other coils flipped. To maintain patient blinding, the sham stimulation group will alter the orientation of all coils during both rounds.

Blinding may be deemed appropriate under the following circumstances: (i) the successful completion of the entire trial; or (ii) the occurrence of serious adverse reactions during the study. In such instances, the treatment personnel are required to promptly report the adverse reactions to the principal investigator, who will determine whether to disclose the blinding.

## Date management and monitoring

3

Data will be collected by treatment operators and outcome raters, with participants receiving training prior to the commencement of the trial to ensure the quality of the data. The endpoint assessor will document and authenticate the data on a case report form (CRF), which will remain unaltered; any modifications to the CRF will be signed and dated. The scale assessor will evaluate the data in accordance with standardized norms and recorded videotapes. Following the collection and entry of data into the electronic data collection system, an additional researcher will review the data to verify its accuracy. Once the validity of the data input is confirmed, the database will be locked; the individual responsible for the subject will have the ability to view and modify the data, while access will be restricted for others.

The Data Monitoring Management Committee, which is composed of members from the Department of Scientific Research at the First Affiliated Hospital of Xi’an Jiaotong University, is responsible for overseeing the data. This committee operates as an independent third party, separate from both the investigator and the sponsor, and maintains no conflicts of interest in relation to this study. The committee will conduct a comprehensive analysis of the research data biannually to ensure its quality.

## Safety monitoring

4

Prior to the experiment, investigators will inform all enrolled patients of the possible benefits and risks and have them sign an informed consent form.

TMS may lead to adverse events, including headache, localized discomfort at the stimulation site, hearing loss, tinnitus, seizures, and syncope. Consequently, several preventive measures are recommended: the use of earplugs during TMS therapy, discontinuation of treatment in the event of headache or localized discomfort, careful monitoring of symptom changes, and the administration of analgesics as needed. Although epileptic seizures are rare during TMS, if seizures or syncope occur, it is imperative to immediately cease stimulation, assess the patient’s vital signs, and conduct further medical evaluations after the seizure has resolved. In instances of discomfort during the procedure, treatment should be halted immediately, followed by clinical observation and symptomatic management (47).

The Ethics Committee of the First Affiliated Hospital of Xi’an Jiaotong University will oversee the safety of this study and provide guidance as needed. In the event of an adverse occurrence, subjects must receive prompt medical attention. Detailed documentation of the adverse event—including its name, time of occurrence, duration, severity, therapeutic measures undertaken, and treatment outcomes—should be meticulously recorded and reported to the Research Safety Supervisory Committee in a timely manner. If necessary, blinding procedures will be implemented in accordance with established protocols. The attending physician will evaluate the causal relationship between the treatment interventions and any adverse outcomes, and will determine whether the patient should continue with follow-up treatment based on the specific circumstances.

## Statistical analysis

5

In this study, we will conduct an analysis of the data utilizing the principles of modified intention-to-treat (ITT) analysis, which will encompass patients who have completed a baseline assessment of the primary outcome indicators. Safety analyses will be performed on all patients who have received at least one session of TMS. Continuous variables will be expressed as the mean ± standard deviation (SD) or median (25th percentile, 75th percentile), while categorical variables will be presented as percentages (%). For the assessment of baseline characteristics, continuous variables will be analyzed using One-way ANOVA (normal distribution) and Kruskal-Wallis H test (non-Gaussian distributions). Categorical variables will be evaluated using Chi-square or Fisher’s exact tests. The primary outcome measure will be the mean change from baseline over a period of 4 weeks, assessed at days 1, 5, 10, D10-24 h, then at weeks 1, 2, 3, and 4, specifically focusing on the average tremor score derived from the TETRAS. We will employ generalized estimating equations (GEE) for repeated measures within the modified ITT population. Additionally, sensitivity analyses will be conducted on the primary outcome, considering age, sex, disease duration, and baseline tremor score as covariates. Effects will be expressed as estimates along with 95% confidence intervals (CIs). GEE will also be applied to analyze secondary outcome measures, including the mean change in tremor power, amplitude, and frequency as recorded by accelerometers.

For data that is randomly missing between TMS sessions, where the missing data constitutes less than 5% of the sample, we will employ the last observation carried forward method to impute the missing values. Additionally, sensitivity analyses will be conducted to evaluate the impact of these imputations on the study outcomes. Conversely, missing data resulting from early dropouts (before 4 weeks) will not be imputed, as this data is not considered to be missing at random. Instead, these instances of missing data will be censored at the date of the participant’s last visit. All statistical analyses will be performed using IBM SPSS version 27.0, and *p*-values less than 0.05 will be considered statistically significant (two-tailed).

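### With about eight patients per arm, GEE run in its ordinary uncorrected form would reject a true null in roughly 9% (pairwise) to 12% (overall) of trials rather than 5%, and its 95% intervals would be too narrow

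*Protocol article*

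**What the plan says.** The method is in section 5, Statistical analysis: "We will employ generalized estimating equations (GEE) for repeated measures within the modified ITT population". The outcome is change from baseline in TETRAS, "assessed at days 1, 5, 10, D10-24 h, then at weeks 1, 2, 3, and 4", which is eight post-baseline visits. The same section extends the method to tremor power, amplitude and frequency: "GEE will also be applied to analyze secondary outcome measures". On reporting it says "Effects will be expressed as estimates along with 95% confidence intervals (CIs"), and on the threshold, p-"values less than 0.05 will be considered statistically significant (two-tailed"). A sensitivity analysis adds age, sex, disease duration and baseline tremor score. SPSS 27.0 is the only software named.

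On size, the abstract says "Twenty-four patients with ET will be randomly assigned to three groups: dual-target stimulation, single-target stimulation, or sham stimulation", and section 2.8 says "our objective is to recruit eight patients per group". Section 2.9 adds that "a simple randomization method will be used to generate 30 random numbers utilizing a table of random numbers", so the arms need not come out equal.

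The article does not state the variance estimator, the working correlation, the reference distribution, or whether the main test is a pairwise contrast or an overall three-arm test. It does not call the p-values descriptive.

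**The concern.** GEE inference is justified when there are many independent clusters. Here the clusters are patients. Eight visits per patient add measurements but no clusters. Two things go wrong when arms are this small. The ordinary sandwich variance is biased low, because it averages squared residuals over n where n − 1 would be needed. The normal or chi-square reference also ignores how poorly that variance is estimated from so few patients. Both errors push the same way: p-values too small and intervals too short.

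At stake is whether a result called significant at 0.05, or a 95% interval, means what it says. Section 6 of the article notes that earlier studies of TMS in essential tremor conflict and that sham stimulation was also followed by improvement. In that setting a false positive would be hard to recognise.

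**Working it through.** **Inputs from the article.** 24 patients, three arms, target 8 per arm; 8 post-baseline visits; two-sided 0.05; 95% intervals; simple randomization; four covariates in the sensitivity analysis. There is no power or error-rate calculation to reproduce. The only stated figure is the nominal level of 0.05.

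**Assumptions not in the article.** Complete data; within-patient correlation exchangeable 0.6 or AR(1) 0.8; normal errors, with a skewed variant; and, for the main figures, an uncorrected sandwich with a normal or chi-square reference.

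**Closed form, one pairwise contrast, 8 v 8.** With complete data and group plus visit effects, the group contrast is the difference between two arms' averages of patient means. It therefore does not depend on the within-patient correlation.
- Sandwich variance of the contrast: (7/8) × (s₁² + s₂²)/8, where s² is the usual variance of patient means with divisor n − 1.
- Wald statistic: √(8/7) × t, with t on 14 df under normal errors with equal variance.
- Rejection when |t₁₄| > 1.960 × √(7/8) = 1.833.
- Size: 2 × P(t₁₄ > 1.833) = **0.088**.

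The same formula gives 9.5% with 7 per arm and 7.9% with 10 per arm.

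**Interval width.** The effective multiplier is 1.833. The t₁₄ multiplier is 2.145, so the ratio is 1.833/2.145 = 0.855. Against t₂₁ (24 − 3 df) it is 1.833/2.080 = 0.882. The intervals are about 12–15% too narrow.

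**Simulation under the null**

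| Setting (uncorrected sandwich) | Pairwise | Overall, 2 df |
|---|---|---|
| 8/8/8, exchangeable 0.6 | 8.7% | 11.7% |
| 8/8/8, AR(1) 0.8 | 9.1% | 11.9% |
| 8/8/8, skewed errors | 8.5% | 12.0% |
| Simple randomization of 24 | 10.2% | 13.3% |
| 7 per arm | 9.5% | 13.0% |
| 10 per arm | 7.9% | 10.0% |
| Four covariates, 8/8/8 | 13.3% | 19.1% |

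Each row rests on 20,000 runs, so the Monte Carlo margin near 9% is 1.96 × √(0.09 × 0.91/20,000) ≈ 0.4 percentage points. The covariate row was run on patient-level data. A smaller set of fitted GEE models with four covariates (under 1,000 runs) gave 11.7% pairwise.

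**Fitted GEE models** (exchangeable working correlation, group and visit effects, 1,500 and 2,000 runs, margin about 1.3–1.5 points). The sandwich with a normal reference rejected in 9.4% of trials, and 95% interval coverage was 90.6%.

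**Other readings of the plan**
- Model-based standard errors with a normal reference: 2 × P(t₂₁ > 1.960) = 6.3% if the patient-level variance uses N − 3. With divisor N it is 2 × P(t₂₁ > 1.833) = 8.1%. Fitted GEE gave 8.2–8.4%.
- Uncorrected sandwich with a t₂₁ reference: 7.1–7.4%.

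**After correction**
- A t-based analysis of patient means: 4.9%.
- Bias-reduced sandwich in fitted GEE: 4.7% with a normal reference and 3.5% with t₂₁.
- A simpler n/(n − 1)-type correction with t₂₁: 5.3–5.8% at 8 per arm and 6.6% under simple randomization.

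**The case against.** The strongest reply is that the article never mentions a Wald test or a sandwich variance. It is a condensed account, and the variance estimator and degrees of freedom normally belong in an analysis plan that is not shown here. This stands in part. The 9–12% range is conditional on the ordinary form of GEE, and it joins two different tests: about 9% for one contrast and about 12% for the overall test. It does not dispose of the point. The method, the 0.05 rule, the interval level and the sample size are all fixed in the text, and every uncorrected variant tried exceeds 5%.

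The second reply is that this is a pilot. Section 2.8 and the Discussion say so, and no go/no-go rule depends on the p-value. That lowers the weight. However, section 2.1 describes a Phase 2 trial meant to evaluate efficacy, and section 5 applies a significance threshold without qualification.

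Three stronger readings are tempting, and the documents do not support them:
- A reader might infer that the trial will certainly run at a 9–12% error rate. The text does not rule out a small-sample correction.
- A reader might add the much larger error rates of a group-by-visit test, or of taking any significant result among several pairwise comparisons. The article plans neither. The first does not match an outcome averaged over visits, and the second is a separate multiplicity question.
- A reader might conclude that the Phase 3 sample size would be wrong. With balanced, complete data the variance correction changes neither the point estimate nor the SD. What suffers is the stated precision of the effect.

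**Conclusion.** The point holds in conditional form, as a should-fix. At about eight patients per arm, ordinary uncorrected GEE would reject a true null in 8.8% of trials for a pairwise contrast and about 12% for the overall group test. Under simple randomization these become about 10% and 13%. With model-based standard errors the rate is about 6–8%. Sandwich-based 95% intervals would be about 12–15% too narrow. The covariate-adjusted sensitivity analysis is affected more (about 12–13% pairwise), so it would not serve as a check on the primary result.

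The 8.8% is exact for 8 v 8 with complete data and normal errors of equal variance. It moved little across the correlation and skewness settings tried. The direction of the error is the same under every uncorrected reading of the plan; its size depends on which one is used.

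**What to change.** Keep the outcome, visits and sample size, and name a small-sample basis for inference before the database is locked.

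- **Preferred:** a linear mixed model for repeated measures, with the group contrast averaged over the eight post-baseline visits and Satterthwaite or Kenward-Roger degrees of freedom. It uses the visits that patients did attend, which suits the plan not to impute early dropouts, although it then relies on a missing-at-random assumption that section 5 does not make for them. The covariance structure should be sparse: an unstructured matrix for eight visits has 8 × 9/2 = 36 parameters, more than the 24 patients.
- **If GEE is kept:** a bias-corrected sandwich variance (Mancl-DeRouen or Kauermann-Carroll) with a t or F reference. Some combinations are mildly conservative (3.5% in the check above).
- Apply the same rule to the accelerometer outcomes and to the covariate-adjusted sensitivity analysis.

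The cost is slightly wider intervals and larger p-values. It must also be confirmed that SPSS 27.0 offers the chosen correction; if not, this analysis should be run in another package and the software statement changed. Recruitment was still open when the article was submitted, so the change could be made before any outcome comparison.

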#### Primary outcome

2.7.1

The primary outcome measure will be the mean change from baseline over the course of 4 weeks (at days 1, 5, 10, D10-24 h, then at weeks 1, 2, 3, and 4). This assessment will focus on the average tremor score derived from the TETRAS. The TETRAS (45) is a widely utilized instrument for evaluating the severity of ET and is employed to assess the remission and recovery of ET following TMS. The scale comprises a 12-item section that evaluates activities of daily living and a 9-item section that assesses tremor severity. Each item is rated on a scale from 0 to 4, with higher scores indicating greater severity.

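### The primary GEE on TETRAS change appears not to adjust for baseline TETRAS; on assumed correlations of 0.5 to 0.9, adjusting would cut the contrast variance by about 42% to 4% net

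*Protocol article*

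**What the plan says.** Under Primary outcome the article states: "The primary outcome measure will be the mean change from baseline over the course of 4 weeks", assessed "at days 1, 5, 10, D10-24 h, then at weeks 1, 2, 3, and 4", which makes eight post-baseline assessments. Under Statistical analysis the model is given as follows: "We will employ generalized estimating equations (GEE) for repeated measures within the modified ITT population". No model terms are listed. The next sentence, worded as an addition to that model, says that "sensitivity analyses will be conducted on the primary outcome, considering age, sex, disease duration, and baseline tremor score as covariates". GEE is also planned for the accelerometer outcomes (power, amplitude, frequency), and no baseline covariate is mentioned for them.

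Two design features bear on this. Under Sample size, "our objective is to recruit eight patients per group", 24 in all. Under Randomization, "a simple randomization method will be used", with no stratification on tremor severity described. Statistical analysis also limits the modified ITT population to patients with a baseline assessment of the primary outcome, so the covariate would be present for every patient analysed.

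**The concern.** A change score uses baseline, but it subtracts it with a fixed slope of 1. When baseline and follow-up are imperfectly correlated, the slope that best predicts follow-up is smaller, so subtraction over-corrects. There are two consequences. The contrast between arms carries avoidable noise. And when one arm happens to start more severe, regression to the mean makes that arm appear to improve more.

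With about eight patients per arm and no stratification, noticeable chance differences in baseline are to be expected. The primary contrast will be tested at a two-sided 0.05 level, and under Sample size the results are meant to inform a Phase 3 power calculation. Loss of precision in the primary estimate therefore carries into the next trial.

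**Working it through.** **The plan's own figure.** 3 groups x 8 = 24 agrees with the total in the Abstract. It rests on precedent from earlier pilot studies. No effect size, SD, correlation or power is given, so there is no calculated figure to reproduce.

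**Inputs from the article.** k = 8 post-baseline assessments; 8 patients per arm; N = 24; g = 3 groups.

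**Assumption, not in the documents.** Unit variance at every visit and one correlation r between all visits, baseline included. The range examined is r = 0.5 to 0.9, plus 0.95.

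**Variance per patient.**
- Mean of the eight follow-ups: P = (1 + 7r)/8.
- Change score: P + 1 - 2r, which simplifies to 9(1 - r)/8.
- Baseline-adjusted: P - r².
- Share of the contrast variance removed: (1 - r)² / (P + 1 - 2r) = 8(1 - r)/9.

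**Cost of estimating one covariate.** The adjusted variance is multiplied by (N - g - 1)/(N - g - 2) = 20/19.

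Example at r = 0.7: P = 5.9/8 = 0.7375. Change score: 0.7375 + 1 - 1.4 = 0.3375. Adjusted: 0.7375 - 0.49 = 0.2475. Ratio 0.733, so 26.7% is removed. Net ratio 0.733 x 20/19 = 0.772, so 22.8% is removed.

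| r | Change score | Adjusted | Removed | Removed, net |
|---|---|---|---|---|
| 0.5 | 0.5625 | 0.3125 | 44.4% | 41.5% |
| 0.6 | 0.4500 | 0.2900 | 35.6% | 32.2% |
| 0.7 | 0.3375 | 0.2475 | 26.7% | 22.8% |
| 0.8 | 0.2250 | 0.1850 | 17.8% | 13.5% |
| 0.9 | 0.1125 | 0.1025 | 8.9% | 4.1% |
| 0.95 | 0.0562 | 0.0537 | 4.4% | -0.6% |

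A simulation of 20,000 trials per value, with eight per arm and patient mean change compared with and without baseline as covariate, gave net reductions of 40.8%, 24.1%, 13.9% and 4.3% at r = 0.5, 0.7, 0.8 and 0.9.

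**If the correlations are not equal.** Suppose follow-up visits correlate more strongly with each other than with baseline. Before the covariate cost, the reduction is 30.3% (0.8 among follow-ups, 0.5 with baseline), 17.6% (0.9 and 0.7) and 12.8% (0.9 and 0.8). These are smaller than the table gives for the same baseline correlation.

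**Chance imbalance.** The baseline difference d between two arms of eight has SD sqrt(2/8) = 0.5 baseline SD. Under normality |d| exceeds 0.5 SD with probability about 32%, and 1 SD with probability about 4.6%. This takes eight per arm as given, which simple randomization does not guarantee.

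**Shift given that imbalance.** The change-score contrast moves by (1 - r) x d towards the arm that started worse. For d = 0.5 SD:

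| r | Shift |
|---|---|
| 0.5 | 0.5 x 0.5 = 0.25 SD |
| 0.7 | 0.3 x 0.5 = 0.15 SD |
| 0.8 | 0.2 x 0.5 = 0.10 SD |
| 0.9 | 0.1 x 0.5 = 0.05 SD |

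**The case against.** Four points deserve weight.

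*The omission is inferred.* The article lists no terms for the primary GEE, and the full plan is not shown. That stands as a limit on certainty: the primary model appears to be unadjusted, and no more can be said. Yet the point is not simply something left to another document, because the article itself assigns baseline score to the sensitivity analyses. If the full plan does adjust the primary model, the article describes it wrongly and still needs the same sentence.

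*The estimate is not biased.* A reader might infer that leaving baseline out biases the primary result, or leaves the whole imbalance in it. Neither follows. Over repeated randomizations the change-score contrast is unbiased. In a given trial only the fraction (1 - r) of the imbalance remains, because the outcome already subtracts baseline.

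*The planned adjusted analysis may be good enough.* A reader might suppose that four covariates are too many for 24 patients to be of use. The arithmetic does not bear this out. With four covariates the cost factor is 20/16 = 1.25. Even if age, sex and duration explain nothing, the variance ratio against the unadjusted change score is 0.69, 0.81, 0.92, 1.03 and 1.14 at r = 0.5 to 0.9. Such a model is therefore more precise than the unadjusted one until 8(1 - r)/9 = 0.2, that is r = 0.775. Nor does the wording settle whether the four covariates enter together. This objection largely stands: a baseline-adjusted estimate will exist, and the issue is which analysis is primary.

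*This is a pilot.* No power is claimed, so no stated operating characteristic is broken. That lowers the severity but does not remove the point.

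**Conclusion.** The point holds in a limited form. As the article reads, the primary GEE does not use baseline TETRAS as a covariate, and it gives up precision over most of the assumed range. The gain at stake is large at r = 0.5, about a quarter of the variance at r = 0.7, and negligible from r = 0.9 upwards. These percentages are shares of the variance of the treatment contrast. They rest on an assumed correlation structure and are not properties of this trial that the documents establish. The Discussion describes within-person variation in tremor and names anxiety, fatigue and caffeine as influences. That would argue against a very high r, but it supplies no value.

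The conditional shift matters mainly at lower r: 0.25 SD for a 0.5 SD imbalance at r = 0.5, against 0.05 SD at r = 0.9. Severity is modest. The change is worth making because it is cheap, not because the planned analysis is invalid.

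**What to change.** In Statistical analysis, state that the primary GEE includes baseline TETRAS as a prespecified covariate. Keep the unadjusted model, and the model that adds age, sex and disease duration, as sensitivity analyses. Adjust each accelerometer outcome for its own baseline value. Study design says that recruitment was ongoing at submission, so the change should be made and dated before unblinding.

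The cost is one sentence and one degree of freedom. No new data are needed. The downside is little or no gain in precision if r is 0.9 or higher, with a very slight loss (0.6% of the variance) at r = 0.95.
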